#### Data collection following recruitment

All medications received by the patients during ICU stay are registered. Every day the amount of kilocalories, lipids, proteins, carbohydrates delivered by either PN or EN are calculated from the PDMS in an automated manner and entered into the case report form (CRF). For calculation of the energy requirements, 50% of the gastric residual volume, which is being discarded by the bedside nurses, is considered to be EN calories not absorbed by the patient. Interruptions of EN delivery and predefined digestive intolerance are registered daily. Mechanical complications such as displacement or obstruction of the enteral feeding tube or the central venous catheters; and clinical complications such as pneumothorax, hemothorax and subclavian or carotid artery puncture are recorded daily. Number of ICU days with a central line in situ is also noted. In addition we record the need for and the number of days of mechanical ventilatory support, of mechanical and pharmacological hemodynamic support, of renal replacement therapies and placement of tracheostomy.

Blood samples (a subset of which are immediately stored on ice for future endocrinological measurements) are taken upon ICU admission and daily at 06:00 h until discharge from ICU or death. All whole blood glucose levels are measured on arterial blood using a blood gas analyzer on each ICU and are registered for later calculation of glucose metrics.

Analyses on blood and urine for the primary clinical analyses include routine chemistry, hematology, and markers of inflammation. Further metabolic, endocrine and inflammatory measurements planned on stored samples in the context of mechanistic analyses fall beyond the scope of this paper. In addition, for later mechanistic studies, a random selection of patients are prospectively and repeatedly screened for the presence of sludge or cholecystitis on ultrasonography.

All new infections of the lungs, the blood stream, the urinary tract and wounds are recorded by an infectious disease specialist. Bacteraemia is further classified by responsible pathogen and as catheter related blood stream infection versus other bacteraemia [33,34].

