**Figure 3 F3:**
[figure not shown]
**CONSORT flow diagram**.

To assess compliance with the study protocol, the amounts of PN and EN actually given in the two study groups during the intervention window of 8 days will be reported as absolute numbers and percentages of target calories.

Discrete variables will be summarized by frequencies and percentages. Continuous variables will be summarized by use of either mean or standard deviations (SD) or median and interquartile range as appropriate.

Baseline and outcome variables will be compared using Student's t-test, (exact) Chi-square test and Mann-Whitney-U test, as appropriate.

All outcomes will be analyzed in an uncorrected manner as well as jointly corrected for risk factors (type and severity of illness, age, BMI and NRS categories). Type of illness will comprise the diagnostic categories, as stratified and grouped per organ system, as well as the presence or absence of a history of cancer. As severity of illness score for this correction, APACHE II will be used. BMI will be categorized as <20, 20-<25, 25-<30, 30-<40 and ≥40 kg/m2. Applicable NRS categories for this study are 3, 4, 5, 6 and 7. In case certain categories would appear underrepresented, such patients will be assigned to the next category in rank or previous category if it is the last category that is underrepresented.

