### Secondary efficacy endpoints

All analyses will be performed uncorrected as well as corrected for age, BMI & NRS categories type and severity of illness. Time to event analysis will be analyzed similarly as the primary endpoint. Proportion of patients requiring support of vital organ functions and distribution of duration of support will be analyzed by non-parametric or parametric testing depending on the normality of the distribution in the subgroup of patients for which support was needed. Proportions will be compared using chi-square testing. Results of repeated measurements will be analyzed using an appropriate model for longitudinal data.

a. Time to discharge alive from the hospital, with patients still in the hospital at closing of the data file censored at that time point; patients transferred to another hospital censored on the day of transfer; and non-survivors censored beyond the longest hospital stay of survivors and censoring time of patients still in the hospital at closing of the data file (90 days after last patient inclusion) over both treatment groups.

b. Time to final (alive) weaning from mechanical respiratory support with patients still on mechanical respiratory support at closing of the data file being censored at that time point and ICU non-survivors censored beyond the longest duration of mechanical respiratory support of the survivors and censoring time of patients still on mechanical respiratory support at closing of the data file (90 days after last patient inclusion) over both treatment groups.

c. Kidney failure: Proportion of patients in need for renal replacement therapy (RRT) during ICU stay; distribution of duration of RRT (for those patients requiring RRT); proportion of patients with a post-randomization diagnosis of new kidney injury/failure (defined by modified Risk, Injury, Failure, Loss, and End-stage Kidney (RIFLE) classification criteria as a plasma creatinine doubling or more during ICU stay) in both treatment groups.

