d. Need for pharmacological or mechanical hemodynamic support during ICU stay, and duration of such need. In addition, time to final (alive) weaning from all pharmacological or mechanical hemodynamic support in ICU will be analyzed, with ICU non-survivors censored beyond the longest duration of pharmacological or mechanical hemodynamic support of the survivors and censoring time of patients still on such support at closing of the data file (90 days after last patient inclusion) over both treatment groups.

e. Need for a tracheostomy during ICU stay.

f. Occurrence of infections during ICU stay: Number of patients with new infections and types of infection as specified in the study protocol and the duration of any antibiotics therapy initiated after randomization for those patients requiring antibiotics.

g. Cholestasis and liver dysfunction: Proportion of patients during the time window of the intervention and during the whole ICU stay presenting with cholestasis, defined as total bilirubinemia above 3 mg/dl or an increase to 150% of baseline value of gamma-glutamyltransferase or alkaline phosphatase. An increase of alanine or aspartate transaminases higher than 3 times the upper limit of normal will be considered as a marker of liver cytolytic damage. Proportion of patients presenting with such liver cytolytic damage during the time window of the intervention and during the whole stay in ICU will be compared. More subtle changes in liver enzymes will be analyzed by comparing the distribution of the highest values and the time course of the daily measurements.

h. Inflammation: Effect of the intervention on inflammation will be analyzed by comparing the distribution of the highest value reached during ICU stay and changes from baseline to the highest value and by comparing time profiles of daily C-Reactive Protein values.

i. Distribution of 6 MWD at hospital discharge in both treatment groups will be compared, as well as the proportion of patients unable to perform the test due to clinical reasons.

j. Proportion of patients independent for all ADL functions in both groups will be compared at hospital discharge. Hospital non-survivors will be analyzed as fully dependent for all functions.

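### The corrected analyses of peak CRP and liver enzymes leave out the marker's own admission value, which costs precision but causes no bias

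*Protocol article*

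**What the plan says.** All of this is in the protocol article.

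- **CRP** (Secondary efficacy endpoints, item h). The summary comparisons are specified as "comparing the distribution of the highest value reached during ICU stay and changes from baseline to the highest value". A third analysis follows, "by comparing time profiles of daily C-Reactive Protein values".
- **Liver enzymes** (item g). Subtler changes are assessed by "comparing the distribution of the highest values and the time course of the daily measurements". No change from baseline is planned for these values. Baseline does enter the definition of cholestasis, through "an increase to 150% of baseline value of gamma-glutamyltransferase or alkaline phosphatase".
- **Covariates.** The opening of Secondary efficacy endpoints states: "All analyses will be performed uncorrected as well as corrected for age, BMI & NRS categories type and severity of illness". General rules of the statistical analyses gives the same set, with outcomes "jointly corrected for risk factors (type and severity of illness, age, BMI and NRS categories". Neither list contains the baseline of the marker under analysis.
- **Repeated measurements.** "Results of repeated measurements will be analyzed using an appropriate model for longitudinal data". How baseline enters that model is not stated.
- **Sampling** (Data collection following recruitment). Blood samples are "taken upon ICU admission and daily at 06:00 h until discharge from ICU or death", and the analyses include routine chemistry and markers of inflammation.

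**The concern.** The plan treats the admission value in two extreme ways. The raw peak ignores it, and the change score subtracts all of it. A regression on the admission value lets the data choose the weight, and in large samples it is at least as precise as either. The planned correction does not provide this, because the covariate list is fixed and omits the marker.

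At stake is power to detect modest effects on CRP and liver enzymes. Item g looks expressly for subtle enzyme changes, where precision counts most. A lesser point is that the raw peak and the change respond in opposite directions to a chance baseline difference, so the two CRP tests can point different ways.

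**Working it through.** **The plan's own figure.** No sample size or power is stated for CRP or liver enzymes. The stated total of 4640 (2320 per arm) does reproduce for its own targets. ICU mortality of 20% against 23% has 70.1% power (two-sided chi-square). A one-day difference in ICU stay with SD 13 has 83.5% power (one-tailed t-test, as stated). The present point leaves these figures untouched.

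**Inputs.** From the documents: 2320 per arm, and a significance level of 0.05 for every endpoint. Assumed, because the documents give neither: the baseline-to-peak correlation ρ, taken from 0.2 to 0.7, and equal SDs at baseline and peak. The comparison is of means, for example on the log scale.

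**Variance of the treatment contrast, relative to the raw peak**

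- Raw peak: 1
- Change from baseline: 2(1 − ρ)
- Adjusted for baseline: 1 − ρ²

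The ordering does not need equal SDs. With k = SD(baseline)/SD(peak), the change score has variance 1 + k² − 2ρk. Subtracting 1 − ρ² leaves (k − ρ)², which is never negative. Subtracting 1 − ρ² from the raw-peak variance leaves ρ², also never negative.

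**Power.** The effect that gives the raw peak 80% power is (1.960 + 0.842) × √(2/2320) = 0.082 SD. For variance factor v, power = Φ(2.802/√v − 1.960).

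| ρ | v, change | v, adjusted | Raw peak | Change | Adjusted |
|---|---|---|---|---|---|
| 0.2 | 1.60 | 0.96 | 80.0% | 60.1% | 81.6% |
| 0.3 | 1.40 | 0.91 | 80.0% | 65.8% | 83.6% |
| 0.5 | 1.00 | 0.75 | 80.0% | 80.0% | 89.9% |
| 0.7 | 0.60 | 0.51 | 80.0% | 95.1% | 97.5% |

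Example at ρ = 0.5: 2.802/√0.75 = 3.235; 3.235 − 1.960 = 1.275; Φ(1.275) = 89.9%.

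The change column applies to CRP only. With equal SDs, the change score is less precise than the raw peak when ρ is below 0.5. In general the threshold is k/2, so at k = 0.5 it falls to 0.25.

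**Chance imbalance.** With equal SDs, a baseline difference of δ between arms shifts the raw-peak contrast by ρδ and the change contrast by (ρ − 1)δ, which have opposite signs for 0 < ρ < 1. The standard error of δ is √(2/2320) = 0.029 SD. At ρ = 0.5, an imbalance of one standard error moves the two contrasts by about 0.015 SD each, in opposite directions.

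**The case against.** The strongest reply is that this is a preference about efficiency in supporting biomarkers. Randomisation makes both the raw-peak and the change contrasts unbiased. With 2320 per arm, 80% power on the raw peak already corresponds to only 0.082 SD. At 0.15 SD the raw peak has about 99.9% power, and the change score at ρ = 0.2 still has about 98%. That stands, and it keeps the point minor.

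The size of the gain also rests on assumptions. Neither ρ nor any marker SD is in the documents, and at ρ = 0.2 the gain over the raw peak is under 2 percentage points. The variance factors describe comparisons of means, whereas General rules of the statistical analyses also allows the Mann-Whitney test. The table takes an uncorrected comparison as its reference. Where age, BMI, NRS, and type and severity of illness already explain part of what the admission value would explain, the further gain may be smaller. All of this stands.

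Four stronger readings are tempting, and the documents do not support them:

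- **That the baseline is wasted.** It enters the CRP change score and the cholestasis definition for gamma-glutamyltransferase and alkaline phosphatase.
- **That the daily time-course analyses share the fault.** Their longitudinal model is left open and may include baseline. Leaving that to a fuller plan is not an error.
- **That the protocol expects early PN to harm through inflammation and liver dysfunction.** The Background links liver dysfunction to overfeeding, which it regards as preventable, and does not list inflammation among those disturbances.
- **That two CRP tests at 0.05 are a special defect here.** The article openly applies 0.05 to every endpoint without multiplicity correction, and no decision rule depends on these markers.

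**Conclusion.** The point holds as a small improvement to a stated analysis. The peak comparisons and the covariate list are both written down, so this does not criticise detail that an article may omit. The list leaves out a covariate that the sampling schedule indicates is collected, and including it cannot reduce large-sample precision.

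Under equal variances and an assumed correlation of 0.2 to 0.7, 80% power on the raw peak becomes about 82% to 97.5% with adjustment, against about 60% to 95% for the CRP change score. These figures are illustrations, and the true gain cannot be derived from the documents. The consequence is lost precision in secondary biomarker endpoints. The primary endpoint, the sample size and the stated power are unaffected.

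**What to change.** In items g and h, add the admission value of the same marker, on the log scale, to the existing risk factors in the corrected analyses of the highest CRP and liver-enzyme values. Name this the main peak comparison. Keep the raw peak and the CRP change from baseline as descriptive summaries. It would also help to state how the admission value enters the longitudinal models, although that detail can sit in a fuller plan.

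The cost is a change of wording, since the sampling schedule already provides the data. The one small downside is that patients without an admission value need a missing-baseline indicator or simple imputation, so that they stay in the intention-to-treat comparison.

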### Sample size calculation

The sample size was calculated in order to detect, with at least 80% power and 95% certainty, an increase or decrease in average duration of ICU stay with one day [from a baseline assumed ICU stay of 8 ± 13 (mean ± SD) days and a median of 4 days assuming log-normal distribution; power calculated using one-tailed Student's t-test using the mean and SD for an increase and a decrease with 1 day and confirmed with two-tailed Student's t-test after log transformation]. To concomitantly detect with at least 70% power and 95% certainty an ICU mortality increase or decrease of 3% (assuming a baseline mortality of 20% anticipating a Medical-ICU/Surgical-ICU patients fraction of 25/75%; power calculated with two-tailed chi-square testing), a sample of 4640 (patients 2320 per arm) was considered necessary. We plan to calculate the true power of the study for detection of any eventual smaller difference in these outcomes.

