A priori defined subgroup analyses will be performed for BMI and NRS subcategories. These subgroup analyses are based on the rationale that BMI has been reported to be associated with different risk of outcome in different types of ICU patients which may be due to different handling of nutritional substrates [36-38]. This risk appeared different for patients with overweight or obesity (BMI 25 to <40) versus all other BMI categories (undernourished and normal BMI [BMI <20 and BMI 20-<25] or morbid obesity [BMI ≥ 40]). Therefore BMI will be dichotomized as such to optimize the power of this subgroup analysis. Also patients at higher risk of malnutrition may respond differently to the feeding strategies. Therefore, in this subgroup analysis, NRS will be dichotomized separating the highest risk patients [NRS ≥ 5] from the moderate risk patients [NRS 3 and 4]. Another a priori defined subgroup analysis will be performed for patients admitted to ICU after emergency or elective cardiac surgery as compared with all other patients. The shorter time in ICU of this subgroup may result in the early PN group receiving predominantly extra glucose 20% infusion, without lipids and amino-acids, as compared with the glucose 5% in the late PN group, which may evoke a different response than the full week combined parenteral nutrition. As sepsis is known to aggravate the metabolic disturbances evoked by early PN, a priori subgroup analysis is planned for patients with and without sepsis upon admission. These a priori defined subgroup analyses will be performed for the primary and safety endpoints without correction for other variables. To test for interaction between the identified subgroups and the studied intervention, a multivariable analysis (logistic regression or proportional hazard analysis as appropriate) will be performed for each subgroup variable separately and with the subgroup variable, the intervention and their interaction in the model. The interaction will be tested at a significance level of 0.1.

The first clinical report will analyze the impact of the nutritional strategies on safety (among which mortality), primary and secondary efficacy endpoints.

For all endpoints, differences will be considered statistically significant whenever the p-value reaches 0.05 or lower without correction for multiple testing.

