### Primary efficacy endpoint

The primary efficacy endpoint for this RCT is the time to discharge alive from ICU. As the time of ICU discharge to the regular ward may be affected by the availability of beds on the regular wards, which could induce bias, we a priori decided to analyze "time to discharge from ICU" as "time to ready for discharge from ICU". A patient is considered "ready for discharge" as soon as all clinical conditions for ICU discharge have been fulfilled (no longer in need for vital organ support and receiving at least 2/3 of the caloric requirements as oral feeds) or earlier when the patient is actually sent to a regular ward.

Time to discharge alive from ICU will be reported by Kaplan Meier plots, with ICU non-survivors censored beyond the longest ICU stay of survivors and censoring time of patients still in the ICU at closing of the datafile (90 days after last patient inclusion) over both treatment groups. The impact of "late PN" versus "early PN" will be analyzed, with and without correction for age, BMI & NRS categories and type and severity of illness, by Cox proportional hazard analysis. The distribution of the actual time to discharge from ICU will be reported for ICU-survivors and ICU-non-survivors separately. In view of the time window of the randomized intervention in ICU, also the proportion of patients staying beyond 8 days in ICU will be reported.

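### The stated power of at least 80% for ICU stay rests on a one-tailed raw-day t-test (74.5% two-tailed) and a log-scale check; neither is the planned Cox analysis, whose power is not given and may be well below 80%

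*Protocol article*

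**What the plan says.** The Sample size calculation section of the protocol article aims to detect, "with at least 80% power and 95% certainty", "an increase or decrease in average duration of ICU stay with one day". The baseline is "8 ± 13 (mean ± SD) days and a median of 4 days assuming log-normal distribution". Two calculations are named: "power calculated using one-tailed Student's t-test using the mean and SD for an increase and a decrease with 1 day", and a second that was "confirmed with two-tailed Student's t-test after log transformation". The same section adds a target of at least 70% power, by two-tailed chi-square test, for a 3-point change in ICU mortality from 20%, and concludes that "a sample of 4640 (patients 2320 per arm) was considered necessary".

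The General rules of the statistical analyses apply one criterion to every endpoint: "differences will be considered statistically significant whenever the p-value reaches 0.05 or lower without correction for multiple testing".

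Under Primary efficacy endpoint, the outcome is time to discharge alive from ICU. It is analysed by Cox regression, "with ICU non-survivors censored beyond the longest ICU stay of survivors". No power is stated for that analysis.

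**The concern.** There are two separate mismatches.

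First, the question is open in both directions and the final test is judged at p ≤ 0.05, but the raw-day power uses a one-tailed test in each direction. Two one-tailed 5% tests amount to a two-sided 10% test, so the result is too favourable for the test that will be run.

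Second, both power calculations treat ICU stay as a duration fully observed in everyone. The planned Cox analysis does not. Patients who die in ICU remain in every risk set, and the plan itself expects them to be 20%. The effect of a change in stay on that analysis can differ greatly from its effect on a t-test.

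This affects how a null result is read. The Discussion says a neutral result would allow PN to be withheld safely in the first week, and the Rationale treats equivalence as evidence for the same strategy. A neutral primary result supports such a reading only as far as the primary analysis could have seen the target difference.

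**Working it through.** **Inputs.** From Sample size calculation: difference 1 day, SD 13, mean 8, log-normal, 2320 per arm, ICU mortality 20%. From General rules: significance at 0.05. From Primary efficacy endpoint: Cox model with non-survivors placed beyond the last discharge.

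**1. The raw-day figure, as planned.** Standard error = 13 × √(2/2320) = 0.3817, so z = 1/0.3817 = 2.62. One-tailed power = Φ(2.62 − 1.645) = 83.5%. The claim of at least 80% is reproduced.

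**2. The same test, two-tailed at 5%.** Power = Φ(2.62 − 1.96) = 74.5%. For 80% power, the detectable difference is 0.3817 × (1.96 + 0.842) = 1.07 days. For one day, n = 2 × (1.96 + 0.842)² × 169 ≈ 2653 per arm, or 5306 in total.

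**3. The log-scale check.** σ² = ln(1 + (13/8)²) = 1.292, so σ = 1.137. The implied median is 4.19 days, close to the stated 4. Standard error = 1.137 × √(2/2320) = 0.0334. With constant CV:
- 8 to 7 days: ln(8/7) = 0.1335, z = 4.00, power 97.9%.
- 8 to 9 days: ln(9/8) = 0.1178, z = 3.53, power 94.2%.

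With SD held at 13, power is above 99.9%. The stated confirmation is reproduced.

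**4. Sample size.** For 20% against 23%, 70% power needs 4630 patients against 4640 stated; 2320 per arm gives 70.1%. The mortality target sets N.

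**5. Why the Cox analysis behaves differently.** With deaths kept at risk, the share not yet discharged alive falls to a floor equal to ICU mortality. If mortality is 20% in both arms, the cumulative discharge hazard ends at −ln(0.20) = 1.61 in both, whatever the lengths of stay. The faster arm's higher early hazard must then be offset by a lower later one, so the effect partly cancels in the Cox estimate.

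**6. Power of the Cox analysis, by simulation.** Log-normal stays, 2320 per arm, deaths beyond all discharges, two-sided 5% score (log-rank) test. A Wald test from a fitted Cox model, run for one scenario, gave 65% against 63–65%. Equal mortality in both arms and death independent of stay are assumptions added here, as is the form of the one-day change.

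| Mean stay | Spread | No deaths | 20% deaths in both arms |
|---|---|---|---|
| 8 to 7 | constant CV | 95% | 32–33% |
| 8 to 9 | constant CV | 90% | 25–26% |
| 8 to 7 | SD 13 | above 99% | 63–65% |
| 8 to 9 | SD 13 | 99% | 57–58% |

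All four are below 80%; two are below 50%. The no-deaths column shows that the loss comes from how deaths are handled.

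**7. Sensitivity to the added assumptions.**
- Every stay shifted by one day, 20% mortality: 78–80%.
- Death correlated with stay (latent correlation −0.3 to 0.5), 20% mortality: 27–74%.
- 10% mortality in both arms, same correlations and independence: about 48–92%.
- Constant CV with a 3-point mortality change: 94–98% if mortality moves with stay. If it moves against stay, about 13%, and the average test statistic then points away from the stay effect.

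**8. Detectable hazard ratio.** Discharges alive: 0.80 × 4640 = 3712. Under proportional hazards, 80% power corresponds to exp(2 × 2.80/√3712) = 1.096. With deaths kept at risk, a hazard ratio of 1.10 moves the floor from 0.20 to 0.20^1.10 = 0.170. It therefore implies mortality falling from 20% to about 17%, not a change in stay alone.

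**The case against.** The case for the plan is substantial. Every power figure it states is reproduced, and the one-tailed test is openly declared. For a skewed stay whose SD exceeds its mean, the log scale is arguably the better one, and there the two-tailed power is 94% or more. A reader might infer that the 80% claim rests only on a one-tailed test, or that it is an arithmetic error. Neither is supported: 74.5% is the two-sided figure for raw days only. The one-tailed test did not set N, and final testing at 0.05 leaves type I error unaffected.

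A reader might also take 25–65% as the power implied by the plan's own assumptions. It is not. Equal mortality, independence of death and stay, and constant CV or SD are additions, and step 7 shows how much they matter. Nor can it be said that a one-day change would generally be missed more often than found: that holds in two of the four scenarios.

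Finally, keeping deaths at risk is a deliberate choice that stops early death from counting as a short stay. Limited sensitivity to a change in stay alone is a known price of that choice, and a cause-specific model answers a different question.

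All of this stands. It does not supply the missing link: the log-scale check also ignores deaths, so neither calculation shows 80% power for the planned analysis.

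**Conclusion.** The concern holds in limited form and should be fixed. The raw-day power for a two-directional question is 74.5%, not the one-tailed 83.5%. The log-scale check passes, but for an analysis that will not be the primary one. Power for the planned Cox analysis is not shown. Under log-normal stay at 8 ± 13 days, a mean of 7 or 9 in the other arm, 20% mortality in both arms and death independent of stay, it is about 25–33% (constant CV) or 57–65% (SD 13). Those figures are conditional; they are neither a bound nor the plan's own number. The sample size of 4640 and the validity of the primary test are not in question.

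**What to change.** In Sample size calculation:
- Replace the one-tailed raw-day figure with its two-sided value, 74.5%.
- State the power of the two-sided Cox analysis actually planned, giving the assumptions on mortality in each arm, on the link between death and stay, and on the form of the one-day change.
- If a detectable hazard ratio near 1.10 is quoted, say that it implies a mortality difference as well.

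In Primary efficacy endpoint, add a cause-specific Cox model, with non-survivors censored at death, as a supporting analysis only and reported beside mortality. Its simulated power in the four scenarios was about 81–98%, but this depends on when deaths occur, which the document does not give.

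In the Discussion, do not let a neutral primary result alone stand as showing no one-day difference in stay.

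The cost is a less favourable stated power, some wording and one extra model on existing data. No extra patients are needed.
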